**Fig. 2 Fig2:**
[figure not shown]
Safety evaluation in 6 to 12 patients with PS of 2

• Patients will be considered to have dose limiting toxicities (DLTs) if durvalumab treatment is interrupted more than two times owing to >Grade 2 pneumonitis or the occurrence of >Grade 3 adverse events.

• The DLTs will be evaluated during the period of 8 weeks after the administration of durvalumab 4 times.

• If < 2 patients show DLTs, durvalumab will be deemed to be safe, and the inclusion of more patients with a PS of 2 will be restarted.

• If 3 DLTs are observed in the first 6 patients, 6 more patients will be included; then, if fewer than 5 of the 12 patients experience a DLT, the enrollment of patients with a PS of 2 will be restarted. Of the 12 patients, if 6 or more experience a DLT, further enrollment of patients with a PS of 2 will be stopped.

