6	Patients with severe malabsorption syndrome or with disease affecting digestive function such as total gastrectomy or active inflammatory bowel disease
7	Patients that have received systemic administration of steroids at a dose of more than prednisolone10mg (or equivalent to this) for 4 weeks or longer
8	Besides the above-mentioned cases, those with contraindications for therapy with carboplatin
9	Patients with active double cancers other than intramucosal carcinoma
10	Mixed small cell and non-small cell lung cancer histology
11	Any concurrent chemotherapy, immunotherapy, biologic or hormonal therapy for cancer treatment. NOTE: Local treatment of isolated lesions, excluding target lesions, for palliative intent is acceptable (eg, by local surgery or radiotherapy)
12	Active or prior documented autoimmune disease within the past 2 years. NOTE: Patients with vitiligo, Grave ‘s disease, or psoriasis not requiring systemic treatment (within the past 2 years) are not excluded.
13	Active or prior documented inflammatory bowel disease (eg, Crohn ‘s disease, ulcerative colitis)
14	History of primary immunodeficiency
15	History of organ transplant that requires therapeutic immunosuppression
16	History of another primary malignancy within 5 years, except for adequately treated basal or squamous cell carcinoma of the skin or cancer of the cervix in situ and the disease under study
17	Other cases that are determined to be inappropriate by attending physicians

**Table 2 Tab2:** Additional inclusion and exclusion criteria in the second registration

Inclusion criteria	
1	Completion of thoracic irradiation with more than total 40 Gy
2	Daily carboplatin with more than 10 day
3	Non-PD and PS 0, 1 or 2 after chemoradiotherapy
4	Normal main organ functions in the following values; Absolute neutrophil count > 1500/mm3, Platelet count ≥100,000/mm3, Hemoglobin ≥9.0 g/dl, AST, ALT ≤2.5 times ULN if no demonstrable liver metastases or ≤ 5 times ULN in the presence of liver metastases, Total bilirubin ≤1.5 times ULN if no liver metastases or ≤ 3 times ULN in the presence of documented Gilbert’s Syndrome [unconjugated hyperbilirubinaemia] or liver metastases, Creatinine within the normal value in each institution, PaO2 or SpO2 ≥ 70 Torr or ≥ 95%
Exclusion criteria	
1	Patients with locally advanced NSCLC who have progressed whilst radiotherapy concurrent with daily carboplatin
2	Any unresolved toxicity CTCAE >Grade 2 from the prior chemoradiation therapy

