3	Patients with any grade pneumonitis from prior chemoradiation therapy
4	Uncontrolled intercurrent illness including, but not limited to, ongoing or active infection, symptomatic congestive heart failure, uncontrolled hypertension, unstable angina pectoris, cardiac arrhythmia, active peptic ulcer disease or gastritis, active bleeding diatheses including any patient known to have hepatitis B, hepatitis C or human immunodeficiency virus (HIV), or psychiatric illness/social situations that would limit compliance with study requirements or compromise the ability of the patient to give written informed consent
5	Receipt of live attenuated vaccination within 30 days prior to study entry or within 30 days of receiving Durvalumab
6	Recent major surgery within 4 weeks prior to entry into the study (excluding the placement of vascular access) that would prevent administration of Durvalumab.

Abbreviation: *PD* progressive disease; *PS* performance status; AST,; ALT,; NSCLC, non-small cell lung cancer; CTCAE,

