### Treatment schedule

Daily, intravenous, low-dose carboplatin (30 mg/m^2^ in a 30-min infusion) is administered 1 h before radiotherapy for the first 20 fractions. Planned radiotherapy of 60 Gy is administered as 30 fractions from 6 to 9 weeks. Radiotherapy is administered 5 days per week (i.e., Monday to Friday with the weekend off) in 2 Gy daily fractions via 6–18 MV X-rays. Both three-dimensional conformal radiotherapy and intensity-modulated radiotherapy are acceptable. Radiation doses are prescribed according to the planning target volume. Motion management is performed as required, and the internal target volume, clinical target volume, and planning target volume vary according to the motion management method used. The use of positron emission tomography (PET) or computed tomography (CT) and four-dimensional CT for radiotherapy planning is encouraged. The gross tumor volume is defined as the primary tumor and any regionally involved nodes on CT (> 1 cm on the short axis) or pretreatment PET (standardized uptake value > 3). The internal target volume is defined as the envelope that encompassed the gross tumor volume plus the ventilatory motion. The clinical target volume margins are 0·5–1·0 cm beyond the internal target volume. The planning target volume margins are 0·5–1·5 cm beyond the clinical target volume, depending on the use of four-dimensional CT for planning and image-guided radiotherapy for delivery. The V20 (the volume of the lung parenchyma that received 20 Gy or more) needs to be less than 30%.

Durvalumab is administered 1 to 42 days after the patients receive chemoradiotherapy. Durvalumab is intravenously administered at a dose of 10 mg per kilogram of body weight every 2 weeks for up to 12 months.

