### Statistical analysis

The primary endpoint is to evaluate the progression free survival rate of 12 months from the initiation of durvalumab administration. The secondary endpoint is to investigate the time to failure, the rate of therapeutic completion, progression-free survival, 2-year survival rate, objective response rate, safety and exploratory biomarker assessment. In the PACIFIC study, the 12-month PFS rate was 55.6% after chemoradiotherapy followed by durvalumab and 35.3% after chemoradiotherapy alone. In the JCOG0301 study, the 12-month PFS rate was approximately 30% after radiotherapy with daily carboplatin [11]. According to the retrospective study conducted by Arslan et al. [17], the 1-year OS rate of patients with LA-NSCLC with a PS of 2 was approximately 50%. This was lower than the 1-year OS rate for elderly patients with a good PS (70.8%) observed in the JCOG0301 study. The degree of difference in OS between patients with a poor PS (included in the study by Arslan et al.) and elderly patients (included in the JCOG0301 study) is approximately 30%, which could be applied to the difference in PFS between these populations. Therefore, we assumed that a 12-month PFS rate of 35% after radiotherapy with daily carboplatin followed by durvalumab in eligible patients would indicate potential clinical usefulness, whereas a rate of 20% would be the lower limit for indicating clinical usefulness. On the basis of this assumption, our study was designed to have a power of 80% and had an alpha level of 0.1 (two-sided). The target number of patients for this study is 53. Therefore, we assess 58 patients considering the progressive disease (PD) rate after treatment with radiation with daily carboplatin and patients who dropped out. In the JCOG0301 study, the PD rate was 8%, the rate of treatment-related death was 3%, and the rate of Grade 3–4 adverse events was 6%, so we assumed the dropout rate to be 20%. During the first registration, 70 patients will be included; then, we analyze 58 patients included during the second registration. A minimum follow-up of 12 months is needed after the last patient starts treatment with durvalumab.

Safety evaluation:

We are also investigating the safety in the first 6 patients with a PS of 2.

Further enrollment of patients with a PS of 2 will be stopped until the safety is confirmed in these 6 patients according to the following criteria (Fig. 2):

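### Read literally, the DLT rule that gates PS 2 enrolment does not count a Grade 3 pneumonitis that permanently ends durvalumab after dose 2 or 3

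*Protocol article*

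**What the plan says.** The rule is in the protocol article, Methods / design, Statistical analysis, under Safety evaluation.

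- **The gate.** "Further enrollment of patients with a PS of 2 will be stopped until the safety is confirmed in these 6 patients".
- **The DLT definition.** A patient has a DLT "if durvalumab treatment is interrupted more than two times owing to >Grade 2 pneumonitis or the occurrence of >Grade 3 adverse events".
- **The window.** "The DLTs will be evaluated during the period of 8 weeks after the administration of durvalumab 4 times".
- **The action limits.** "If < 2 patients show DLTs, durvalumab will be deemed to be safe"; and "If 3 DLTs are observed in the first 6 patients, 6 more patients will be included".

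The Treatment schedule gives the dosing interval: "Durvalumab is intravenously administered at a dose of 10 mg per kilogram of body weight every 2 weeks for up to 12 months". The printed definition has no separate criterion for permanent discontinuation. It does not say whether an interruption is an episode or a missed dose.

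**The concern.** A DLT rule should capture the toxicity that most clearly limits dosing, namely one serious enough to end treatment. This rule ties pneumonitis to a count of repeated interruptions. A patient whose durvalumab is stopped for good is interrupted once and never restarts, so the worse outcome can score lower than several short holds.

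The adverse-event limb might catch such a patient, but its limit is printed as above Grade 3, which literally leaves Grade 3 out. The window adds a second difficulty: if it opens only once dose 4 has been given, a patient who stops after dose 2 or 3 never enters it.

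At stake is the decision to reopen PS 2 enrolment. Two readers could classify the same patients differently and reach opposite decisions. The plan treats pneumonitis as a risk before durvalumab starts, since Table 2 excludes "Patients with any grade pneumonitis from prior chemoradiation therapy". That criterion concerns chemoradiation and does not settle how pneumonitis on durvalumab is counted.

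**Working it through.** The article states no figure to reproduce here. The check applies the printed rule to one defined case: a single Grade 3 pneumonitis, with no earlier interruption, that permanently ends durvalumab.

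**Inputs**
- One dose every 2 weeks (Treatment schedule), so doses 1 to 4 fall at weeks 0, 2, 4 and 6.
- Pneumonitis limb: grade above 2 and more than two interruptions.
- Adverse-event limb: grade above 3.
- Window: either the first four doses (4 × 2 weeks = 8 weeks), or up to 8 weeks after dose 4 (week 6 + 8 = week 14).

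**Step 1: count the interruptions.** Missed doses = doses due in the window minus doses given. In the last column the lower figure leaves out the week-14 dose.

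| Last dose given | Episodes | Missed, four-dose window | Missed, window to week 14 |
|---|---|---|---|
| 1 | 1 | 4 − 1 = 3 | 6 to 7 |
| 2 | 1 | 4 − 2 = 2 | 5 to 6 |
| 3 | 1 | 4 − 3 = 1 | 4 to 5 |

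**Step 2: pneumonitis limb.** The grade condition is met, because 3 is above 2. If episodes are counted, 1 is not more than two in either window. If missed doses are counted in the four-dose window, only a stop after dose 1 exceeds two; stops after dose 2 (two missed) and dose 3 (one missed) do not. If missed doses are counted to week 14, all three stops exceed two and the event is a DLT.

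Boundary case: if the dose due at week 8 also falls inside the shorter window, a stop after dose 2 misses three doses and counts. A stop after dose 3 misses two and does not.

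**Step 3: adverse-event limb.** Literally, 3 is not above 3, so the event is not counted. It is counted, whatever the unit or window, if the sign means Grade 3 or higher **and** the limb stands alone. If the condition of more than two interruptions also governs this limb, the inclusive sign is not enough by itself.

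**Step 4: literal window after dose 4.** A patient stopped after dose 2 or 3 never receives dose 4. The printed text does not say how that patient is classified.

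**Step 5: effect on the gate.** Suppose three of the first six PS 2 patients have this event and nobody has another DLT. The count is 0 where the event is missed, and enrolment reopens. It is 3 where the event is counted, and six more patients are added.

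**Step 6: illustration with assumed rates.** The article gives no rates, so those below are assumptions. Treat patients as independent and let *p* be the total DLT probability. The chance of 0 or 1 DLT in six is (1 − *p*)⁶ + 6*p*(1 − *p*)⁵.

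- Other DLTs at 10%, event not counted: 0.9⁶ + 6 × 0.1 × 0.9⁵ = 0.531 + 0.354 = 0.886 (before rounding, 0.8857).
- Same, with the event counted at 5%, 10%, 15% or 20% (*p* = 0.15 to 0.30): 0.776, 0.655, 0.534, 0.420.
- Other DLTs at 5%: 0.967 not counted; 0.886 to 0.534 counted over the same event rates.
- Other DLTs at 20%: 0.655 not counted; 0.534 to 0.233 counted.

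**The case against.** The strongest reply is that the article uses inequality signs loosely, so the inclusive reading is probably the intended one. It describes the older group as over 75 in several places, while the title and Table 1 admit patients from 75, and the Discussion once prints the sign for at least 75. In the DLT rule itself, fewer than two is followed by three, and fewer than five of twelve by six or more. If Grade 3 or higher is meant and the adverse-event limb stands alone, the two limbs make clinical sense: repeated holds for milder pneumonitis, or any severe event. Table 2's "Any unresolved toxicity CTCAE >Grade 2 from the prior chemoradiation therapy" stands beside signs that do include equality, which leans towards a strict reading, but it uses the same notation and proves little.

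This stands in part. It makes the inclusive reading quite plausible but does not establish it, and it leaves the scope of the *or* open. Reading the interruption count just as loosely, as two or more, would bring in a stop after dose 2 if missed doses are counted in the four-dose window, but not a stop after dose 3.

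It is also fair that Fig. 2 is not shown, that the full protocol may define interruption and discontinuation, and that the example in step 5 is constructed. An article may leave detail out. Here, however, it prints an operative definition, window and action limits, and the objection is to what those words say.

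A reader might infer that the pneumonitis limb can hardly be met within 8 weeks. The documents do not support that: two delayed doses followed by a permanent stop before dose 4 already make three interruptions.

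**Conclusion.** The point holds for the printed wording and should be fixed. Read literally, the rule lets the PS 2 gate be passed despite treatment-ending Grade 3 pneumonitis after dose 2 or 3. This rests on three conditions: Grade 3 alone is not enough, the patient had no earlier interruptions, and interruptions are counted either as episodes or as missed doses within the four-dose window. Other plausible readings count the event, so the rule does not fix the decision.

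The size is a possible change of decision in one safety gate, from expanding the cohort to reopening enrolment. How often this would happen cannot be derived from the article; the probabilities in step 6 rest on assumed rates.

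A reader might go further and infer that the trial would ignore such a case or that PS 2 patients go unmonitored. The documents do not support this: adverse events are a secondary endpoint and are still recorded, and the full protocol may be clearer. Nor is the primary analysis of 12-month PFS affected. Confidence is medium, because Fig. 2 and the full protocol are not available.

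**What to change.** Reword the definition along these lines:

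*The DLT window is 8 weeks from the first durvalumab dose. A DLT is (a) any adverse event of Grade 3 or higher in the window, pneumonitis included; or (b) any toxicity that permanently stops durvalumab in the window; or (c) more than two interruptions because of pneumonitis of the stated grade or higher.*

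Limb (a) should be written this way if Grade 3 or higher is the intent; otherwise state the intended grade in words instead of with a sign. Limb (b) matters most here: it counts patients who never reach dose 4 because of toxicity, whatever the grade limit. If limb (c) is kept, say whether it counts episodes or missed doses.

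Under this wording the case in step 5 gives a count of 3, and the cohort is expanded.

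The cost is amendment text and no new data. The downside is that more DLTs may be counted and PS 2 enrolment may be held longer. If the full protocol already contains these terms, only the article's wording needs correcting.

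### The written PS 2 safety rule gives no action for 2 DLTs in 6 or 5 in 12, and the enrolment hold makes it stricter on 2 of 6 than on 3 of 6

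*Protocol article*

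**What the plan says.** The Safety evaluation part of the Statistical analysis section singles out the first six PS 2 patients and sets a default: "Further enrollment of patients with a PS of 2 will be stopped until the safety is confirmed in these 6 patients". The bullets under Fig. 2 then give the thresholds.

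- Six patients, restart: "If < 2 patients show DLTs, durvalumab will be deemed to be safe", after which PS 2 inclusion resumes. This covers 0 or 1 DLT.
- Six patients, expand: "If 3 DLTs are observed in the first 6 patients, 6 more patients will be included".
- Twelve patients, restart: "if fewer than 5 of the 12 patients experience a DLT". This covers 4 or fewer.
- Twelve patients, stop: "Of the 12 patients, if 6 or more experience a DLT, further enrollment of patients with a PS of 2 will be stopped".

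The Fig. 2 caption reads "Safety evaluation in 6 to 12 patients with PS of 2". The article gives no expected or unacceptable DLT rate and no operating characteristics for this rule.

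**The concern.** A staged safety rule should assign one action to every possible count, and the actions should become no milder as toxicity rises. The written thresholds do neither. At each stage one count falls between two stated boundaries: 2 of 6, between restart at 0 or 1 and expansion at 3; and 5 of 12, between restart at 4 or fewer and stopping at 6 or more.

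The hold makes the first gap worse than an omission. With 2 of 6, safety has not been confirmed by any listed criterion, so enrolment stays closed and no step follows. With 3 of 6, six more patients enter and the group can reopen.

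The rule decides whether PS 2 patients beyond the safety cohort can enter the trial, and the Discussion presents PS 2 as a population where benefit is unclear and the results are expected to help. If the text governs, either the decision at 2/6 or 5/12 is made after the toxicity has been seen, or the group stays closed on a result milder than one that is allowed to continue.

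**Working it through.** **Step 1: list every outcome against the text.** Twelve patients are reached only after 3 of 6, so the total at 12 runs from 3 to 9.

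| Stage | DLTs | Written action |
|---|---|---|
| 6 patients | 0–1 | restart |
| | 2 | none (hold remains) |
| | 3 | add six |
| | 4–6 | none (hold remains) |
| 12 patients | 3–4 | restart |
| | 5 | none |
| | 6–9 | stop |

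At 4–6 of 6 the hold gives a sensible result that only needs stating. It is not counted as a gap below.

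**Step 2: inputs.** The thresholds come from the article. The true DLT rate p does not, so p = 5, 10, 20, 30 and 40% are assumptions. There is no stated figure to reproduce.

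**Step 3: formulas.** Let b(k) be the binomial probability of k DLTs in six patients at rate p.

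- P(2/6) = b(2)
- P(5/12) = b(3) × b(2), that is 3 in the first six and 2 in the next six
- Restart as written, both gaps left on hold = [b(0) + b(1)] × [1 + b(3)]
- Repair A (2/6 and 5/12 both restart) = [b(0) + b(1) + b(2)] × [1 + b(3)]
- Repair B (2/6 restarts, 5/12 stops) = b(0) + b(1) + b(2) + b(3) × [b(0) + b(1)]
- Repair C (2/6 or 3/6 expands, 4 or fewer of 12 restarts) = b(0) + b(1) + b(2) × [b(0) + b(1) + b(2)] + b(3) × [b(0) + b(1)]

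**Step 4: one case in full, p = 20%.** b(0) = 0.2621, b(1) = 0.3932, b(2) = 0.2458, b(3) = 0.0819.

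- P(5/12) = 0.0819 × 0.2458 = 0.0201
- Either gap = 0.2458 + 0.0201 = 0.266
- As written: 0.6554 × 1.0819 = 0.709
- Repair A: 0.9011 × 1.0819 = 0.975
- Repair B: 0.9011 + 0.0819 × 0.6554 = 0.955
- Repair C: 0.6554 + 0.2458 × 0.9011 + 0.0819 × 0.6554 = 0.931

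**Step 5: all assumed rates.**

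| | 5% | 10% | 20% | 30% | 40% |
|---|---|---|---|---|---|
| P(2/6) | 0.0305 | 0.0984 | 0.2458 | 0.3241 | 0.3110 |
| P(5/12) | 0.0001 | 0.0014 | 0.0201 | 0.0600 | 0.0860 |
| Either gap | 0.031 | 0.100 | 0.266 | 0.384 | 0.397 |
| P(4–6 of 6), not counted | 0.0001 | 0.0013 | 0.0170 | 0.0705 | 0.1792 |
| Restart, as written | 0.969 | 0.899 | 0.709 | 0.498 | 0.298 |
| Restart, repair A | 1.000 | 0.998 | 0.975 | 0.882 | 0.695 |
| Restart, repair B | 1.000 | 0.997 | 0.955 | 0.822 | 0.609 |
| Restart, repair C | 1.000 | 0.996 | 0.931 | 0.739 | 0.467 |

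**Step 6: the inversion.** After 3 of 6, enrolment reopens if at most one of the next six has a DLT, with probability b(0) + b(1) = 0.655 at p = 20%. After 2 of 6 the written rule offers no way to reopen. At p = 20% the unassigned 2/6 is also likelier than the assigned 3/6 (0.246 against 0.082); at 30% it is 0.324 against 0.185.

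**The case against.** The strongest reply is that the text is not the whole rule. The criteria refer to Fig. 2, whose content could not be seen here, and the article condenses a fuller protocol. Either may assign both counts, in which case sites do have a rule. That stands as a limit on the operational harm. It does not rescue the wording. If the figure restarts at 2/6, the first restart threshold is wrong; if it expands there, the expansion threshold is wrong. If it restarts at 5/12, the second restart threshold is wrong; if it stops there, the stopping threshold is wrong. If it is silent on either count, that gap remains.

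A second reply is that this is loose use of strict and non-strict limits, as with the article's varying descriptions of the age cut at 75. That is the likeliest origin. A symbol lost in conversion is a poor explanation: non-strict signs survive in Table 1, and the 12-patient limits are written in words.

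Third, the hold protects patients. This is accepted: 2/6 leads to no further exposure. Whether the hold carries through the expansion to 12 is not stated, so the default at 5/12 is less certain.

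Fourth, the size depends on an unknown DLT rate. If the DLT definition requires repeated durvalumab interruptions whichever the cause, DLTs may be uncommon and the 5–10% columns more relevant; if a severe adverse event counts alone, higher rates are plausible. The 5/12 gap is small by itself.

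**Conclusion.** The concern holds for the criteria as written. Two counts have no stated action and, under the enrolment hold, the milder 2 of 6 is treated more strictly than 3 of 6. This is a stated decision rule that gives a wrong result, not detail left to another document.

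The chance of meeting one of the two gaps runs from 3.1% at a 5% true DLT rate to 39.7% at 40%. At 20%, PS 2 enrolment restarts with probability 70.9% as written and 97.5% if both counts were meant to restart. These figures assume independent DLTs at a common rate, exactly six patients per stage, and a hold that persists at 2/6 and 5/12. The textual defect rests on none of these assumptions. Because this is the safety rule for one of the two eligible groups, it should be corrected before it is relied on.

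**What to change.** State an action for every count, in agreement with Fig. 2, with no lower count treated more strictly than a higher one. The likeliest intention is:

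- 6 patients: 2 or fewer DLTs, restart; 3, add six; 4 or more, stop.
- 12 patients: 5 or fewer, restart; 6 or more, stop.

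If the safety team wants 5 of 12 to stop enrolment, the last line becomes 4 or fewer, restart; 5 or more, stop. If Fig. 2 expands at 2 of 6, the expansion bullet should cover 2 or 3 of 6, and both 12-patient limits should be set to meet.

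The choice is a safety decision. At a true DLT rate of 40%, repairs A, B and C reopen PS 2 enrolment with probability 69.5, 60.9 and 46.7%, so the team should confirm that it accepts the version it adopts. If Fig. 2 already settles the thresholds, the cost is a wording correction to two bullets, with no added patients or procedures. If the full protocol carries the same wording, it needs the same correction.
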